#### Waitlist Control Procedures

For consistency of exposure to research team personnel, both the immediate intervention and waitlist classrooms were visited by the implementation team twice weekly for 20 minutes per week. For the waitlist classroom, implementers interacted with children during typical classroom activities (eg, reading and playing with sensory tables).

Following the 16 weeks of programming and postassessment time point, the waitlist group received 8 weeks of the MMP with each program component sequentially added every 2 weeks. This condition allowed for testing of shorter program dosage effects than longer ones.

#### Data Collection Timeline

Data were collected at 4 time points: baseline (preintervention; all classrooms), midintervention time point (8 weeks into programming; all classrooms), postintervention time point (immediately following the 16-week intervention or waitlist period; all classrooms), and 2-month follow-up (2 months after the intervention; 1 intervention classroom). In the waitlist control group, the postintervention time point also served as their second baseline and the 2-month follow-up served as their postintervention time point (immediately after the 8-week intervention). The data collection time points are illustrated in Figure 1 for the intervention (black) and waitlist control (gray) groups. At each time point, survey data were collected electronically (in person or online) or via paper and pencil, whichever was feasible and preferred by participants. Behavioral assessments were administered at all time points except for the midintervention time point.

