#### Effects on Mechanisms and Outcomes

This aim focused on investigating how the implementation of the MMP influences self-regulatory capacities, SEL skills, problem behaviors, and prosocial behaviors, as well as identifying underlying physiological mechanisms of program effects at the midpoint, postintervention time point, and 2-month follow-up. Physiological data were collected after each MMP component, allowing for the evaluation of the effects of sequential implementation on physiological responses.

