**Report on children**				
	Sociodemographic	Age, sex, race or ethnicity, disabilities, home language, and language proficiency	Parent and teacher	Before intervention
	Adversity	Adverse Childhood Experiences Questionnaire	Parent	Before intervention
	Social-emotional behavior	Children’s Behavior Questionnaire– very short form Strengths and Difficulties Questionnaire Open-ended questions^a^	Parent and teacher	Before intervention, after intervention, and follow-up
	Relationship and implicit bias	Student-Teacher Relationship Scale–short form Preschool expulsion risk measure Open-ended questionsa	Teacher	Before intervention, after intervention, and follow-up

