**Self-report**				
	Sociodemographic	Age, sex, race or ethnicity, highest level of education achieved, household income, marital status, employment status, number of kids, and teachers’ role^b^	Parent and teacher	Before intervention
	Stress level	Perceived Stress Scale	Parent and teacher	Before intervention, after intervention, and follow-up
	Teachers’ changes	Teacher SEL^c^ Beliefs Scale Mindfulness in Teaching Scale	Teacher	Before intervention, after intervention, and follow-up

^a^These were also administered at the midintervention time point.

^b^Data collected only from teachers at follow-up.

^c^SEL: social-emotional learning.

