### Strengths

Strengths of the study include its focus on the crucial early childhood period for emotion regulation and behavioral intervention, the investigation of physiological and behavioral mechanisms undergirding the effects of mindfulness on outcomes, and the exploration of program implementation feasibility and acceptability among diverse early childhood populations. The study uses multiple reporters and data sources to triangulate findings and uses a whole-person approach. Moreover, it examines short-term and sustained effects of programming on teacher and child outcomes. It captures potential dose effects by administering 16 weeks of programming to the intervention group and 8 weeks of programming to the waitlist control group. Finally, it incorporates a train-the-teacher model of implementation that can be tested with follow-up, even for 2 months, to inform the need and frequency for boosters and technical assistance.

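### For tasks, standardized scales and hair samples, only postintervention sets treated against untreated children, so the sustained-effect and dose claims go beyond the design

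*Protocol article*

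**What the plan says.** All statements are in the protocol article.

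- **Aim 2** (Effects on Mechanisms and Outcomes) covers self-regulation, social-emotional skills and behavior, and names "program effects at the midpoint, postintervention time point, and 2-month follow-up". The words just before that quote refer to physiological mechanisms.
- **Midpoint** (Data Collection Timeline; Table 4): "Behavioral assessments were administered at all time points except for the midintervention time point". The repeated standardized scales are scheduled "Before intervention, after intervention, and follow-up". Footnote a of Table 4, attached to the open-ended questions, adds: "These were also administered at the midintervention time point".
- **Follow-up** (Data Collection Timeline): "2-month follow-up (2 months after the intervention; 1 intervention classroom". For the waitlist, "the 2-month follow-up served as their postintervention time point (immediately after the 8-week intervention".
- **Dose** (Waitlist Control Procedures), on the 8-week waitlist program: "This condition allowed for testing of shorter program dosage effects than longer ones". Strengths adds that the 16- and 8-week programs capture potential dose effects.
- **Sustained effects** (Strengths): "it examines short-term and sustained effects of programming on teacher and child outcomes". Limitations says that the follow-up is short and that sustained effects are therefore uncertain.
- **Analysis** (Data Analysis): one-tailed t tests and linear regression are planned for objectives 2 and 3.

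**The concern.** A controlled estimate of a program effect needs treated and untreated children measured with the same instrument at the same time. The article claims effects at follow-up and a dose comparison, but its schedule does not supply that pairing for either.

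The Introduction describes the preschool years as a period of rapid maturation in self-regulation and cognition, so growth is a serious rival explanation for any uncontrolled change. Inferential tests are planned and the data are still being processed. Contrasts the design cannot identify could therefore be tested, reported as sustained or dose effects, and carried into the larger trial this pilot is meant to inform.

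**Working it through.** **Figures that can be reproduced.** The article gives no sample size, power or alpha for these contrasts. The arm shares agree: 22/32 = 68.75% and 10/32 = 31.25%. The baseline age test from Table 1 gives a pooled SD of √[(21 × 0.50² + 9 × 0.72²)/30] = 0.575, a standard error of 0.575 × √(1/22 + 1/10) = 0.219, and t = (4.6 − 3.9)/0.219 = 3.19. Rounding of the means allows 2.74 to 3.65, which covers the stated magnitude of 2.97.

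**Step 1: measure by time point.** Sources are Data Collection Timeline, Table 4, HRV Measurement and Hormone Measurements.

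| Measure | Midpoint | Postintervention | 2-month follow-up |
|---|---|---|---|
| Behavioral tasks | none | both arms, waitlist untreated | one intervention classroom; waitlist treated |
| Standardized scales | none (open-ended questions only) | both arms, waitlist untreated | one intervention classroom; waitlist treated |
| Hair samples | none scheduled | both arms, waitlist untreated | one intervention classroom; waitlist treated |
| Heart rate variability (HRV) | every 4 weeks during implementation; waitlist collection during the wait not described | both arms, waitlist untreated | one intervention classroom; waitlist treated |

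In the first three rows, treated-versus-untreated data after baseline exist only at postintervention.

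**Step 2: follow-up.** Within the one intervention classroom, change from postintervention to follow-up = maintenance or fading + maturation over 2 months. One observed quantity cannot separate two unknowns. Between arms, the follow-up difference = (16-week program effect 2 months later) − (8-week program effect just after delivery) + classroom difference. No term is a program effect against no program.

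**Step 3: dose.** Write E for program effect and G for growth.

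- Intervention arm, baseline to postintervention: E(16) + G(16 weeks, earlier period).
- Waitlist, second baseline to follow-up: E(8) + G(8 weeks, later period).
- Difference: [E(16) − E(8)] + [G(16) − G(8)] + classroom and period differences.

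The 8-week side is one classroom. It starts after the 16 weeks, adds components every 2 weeks instead of every 4, and follows 16 weeks of implementer visits. Each factor changes together with dose. Age differs too: 4.6 − 3.9 = 0.7 years at baseline. When the waitlist program starts, its children average about 3.9 + 16/52 = 4.2 years, so the gap in starting age is about 0.4 years.

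**Step 4: classroom-level information.** Degrees of freedom = classrooms − 2.

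- Postintervention, all classrooms: 3 − 2 = 1.
- Postintervention, randomized site 1 pair: 2 − 2 = 0.
- Follow-up: 2 − 2 = 0.

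With 0 degrees of freedom, classroom variation cannot be separated from the arm difference. Postintervention is weak as well. Assuming classrooms of 11, 11 and 10 and an intraclass correlation of 0.05 to 0.20, a simulated child-level one-sided 5% t test that ignores classroom rejects a true null about 9% to 18% of the time.

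**The case against.** The best defense is that this is an openly exploratory pilot. Strengths says potential dose effects, Limitations calls sustained effects uncertain, the abstract promises only preliminary evidence, and the single follow-up classroom and treated waitlist are stated in the timeline. This makes it a matter of wording and analysis scope. It does not remove the point: the dose sentence in Waitlist Control Procedures is unhedged, and the stated uncertainty is attributed to follow-up length, not to the missing untreated control or the single classroom.

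A second defense is that the waitlist's postintervention assessment doubles as its second baseline. That class therefore has 16 weeks without the program followed by 8 weeks with it, an imperfect but useful within-classroom reference for maturation. This stands, and the fix keeps it.

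A reader might go further and infer that no outcome at all can be compared between arms at midpoint, or that aim 2 flatly contradicts the schedule. The documents do not support that. The time points in aim 2 can be read as belonging to the physiological mechanisms. HRV is listed among the outcome measures and was taken every 4 weeks, and midpoint collection is said to cover all classrooms. Whether the waitlist had HRV during the wait is not stated, and Figure 1, which might show it, is not available. Later hair samples might also be read by segment for earlier months. The point is therefore limited to tasks, standardized scales and scheduled hair samples.

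Nor should a reader infer that the postintervention contrast is sound. It has data from both arms and an untreated control, but only one classroom per arm was randomized and the site 2 classroom was assigned.

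**Conclusion.** The point holds with that scope and should be corrected. At follow-up there are no untreated children and one of two intervention classrooms, so a between-arm difference is not a program effect and a within-classroom change cannot distinguish maintenance from maturation. Dose is fully confounded with classroom, calendar period, window length, component pace and prior implementer contact, and covariate adjustment cannot separate dose from a single classroom. The dose contrast would fail even if both intervention classrooms had been followed up.

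The conclusion rests on the text of the timeline and Table 4. The number of children in the follow-up classroom is not given in the text, and Figures 1 and 2 were not available. The simulated error rates use assumed classroom sizes and correlations and only illustrate the postintervention caveat.

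**What to change.** 1. Restrict between-arm effect estimates for tasks, scales and hair to baseline-to-postintervention. State beside them that one classroom per arm was randomized at site 1 and that site 2 was assigned.
2. Report the 2-month follow-up as uncontrolled, descriptive change in one intervention classroom.
3. Report the waitlist's 8-week change descriptively beside its own 16-week change without the program, not as a dose comparison.
4. Reword the dose sentence in Waitlist Control Procedures and the sustained-effect and dose statements in Strengths.
5. Add the absence of an untreated control at follow-up and the single follow-up classroom to Limitations.
6. State in aim 2 that midpoint outcomes are HRV and open-ended answers, not tasks or scales, and say whether waitlist HRV was recorded during the wait.

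Collection is complete, so this changes only wording and analysis scope. The cost is that two advertised strengths are withdrawn or softened.

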**Figure 1 figure1:**
[figure not shown]
Overview of data collection time points for the experimental group.

### Outcome Measures

#### Behavioral Assessments

The pencil tapping task assessed working memory and inhibitory control [41,42]. In this task, both the evaluator and the child held a pencil in their dominant hand. The child was instructed to tap the pencil twice when the evaluator tapped once and to tap once when the evaluator tapped twice. This required the child to hold the rules in working memory while inhibiting the natural tendency to mirror the evaluator’s tapping pattern. Up to 6 practice trials were used before the official assessment began. During the practice trials, the evaluator provided feedback on correct and missed trials to ensure understanding of the task. Following the practice trials, 16 scored trials were administered without feedback. The total number of correct responses ranges from 0 to 16.

The gift delay task assessed self-regulation [43]. In this study, it also served as a stress task to assess child coping and stress response (eg, behavioral and physiological response via heart rate variability [HRV], respiratory sinus arrhythmia, and vagal efficiency). During this task, the child sat at a table while the experimenter presented a gift bag containing a prize, explaining that the bag needed a bow before the child could open it. The experimenter placed the bag in the center of the table and instructed the child to remain seated and not touch the bag until she returned. After a 3-minute delay, the experimenter returned, placed the bow on the bag, and gave the child the gift, regardless of whether they followed the instructions. Scoring was based on the child’s ability to resist the temptation to touch the gift bag during the waiting period. Children were given a score of 1 if they took the gift from the bag, 2 if they put their hand in the bag, 3 if they peeked in the bag, 4 if they touched the bag, and 5 if they followed all instructions. Scores ranged from 1 to 5. Time spent out of the seat was also calculated and categorized into 4 distinct levels: 1 for <30 seconds in the seat to 4 for >2 minutes in the seat. A final seat score was computed by assigning an additional half point for each minute a child spent out of the seat within arm’s reach of the table for those with scores of 1 or 2. The task was video recorded using a discreet camera for later review and double scoring by a second researcher.

The tower task assessed turn-taking and inhibition [43]. During this task, the child sat at a table with the experimenter seated across from them. The child was given a practice trial where they were instructed that they would be building a tower together by taking turns. First, the experimenter placed a block on the table and instructed the child to place the next block on top. The practice trial ended after the tower was 6 blocks tall. During the practice trial, they were reminded to take turns if they were not taking turns. The actual trial consisted of 12 blocks and the experimenter told the child that they would build a really tall tower together and the child could go first. Children were scored on 2 characteristics. First, on turn-taking: 0 for no turns (children built the tower by themselves), 1 for partial turn-taking, or 2 for full turn-taking. A second turn-taking score was calculated based on the proportion of blocks placed by the experimenter (multiplied by 10) relative to the total number of blocks placed. The child received the highest score if they alternated placing blocks equally with the experimenter. A penalty of 5 points was applied if the child knocked the tower over, while an additional 5 points were awarded if the child gently removed blocks from the tower during cleanup. Children were given 2 minutes to clean up the tower and were scored 2 if they cleaned up the towers on the first try, 1 if they needed follow-up after 1 minute, or 0 if they did not clean up the tower.

The go/no-go task assessed inhibitory control in young children [44-48]. In our study, we used an app-based version of the go/no-go task on an Apple iPad. Children were tasked with catching fish (go trials) and avoiding sharks (no-go trials) as they moved across the screen [49]. To enhance the dominant response and increase the difficulty of inhibiting responses during the “no-go” trials, 80% (n=60) of the trials were “go” trials and 20% (n=15) were “no-go” trials. Before starting, children received instructions on both trial types and practiced 5 trials of each. This was followed by a mixed block of 10 practice trials (with 80% being “go” trials). A brief review of the instructions was provided before the task began. The main task consisted of 75 test stimuli evenly distributed across 3 blocks. The stimuli were presented in pseudorandom order, ensuring that no block began with a “no-go” trial and that no more than 2 consecutive “no-go” trials occurred. A 1000-millisecond interval was maintained between stimuli. Scores were calculated by first excluding trials with response times <300 millisecond, as these were considered non–task related. Next, blocks were removed if the child demonstrated nonresponsiveness (ie, go trials with <20% accuracy or no-go trials with >80% accuracy) or indiscriminate responding (ie, go trials with >20% accuracy and no-go trials with <20%). The impulse control score, which reflects the ability to withhold a response in the presence of a strong, automatic tendency to respond, was calculated by multiplying the percentage of correct “go” responses by the percentage of correct “no-go” responses.

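### The gift delay seat score adds an uncapped credit for time out of the seat within arm's reach, only at scores of 1 or 2, so a child can tie or pass one who sat longer

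*Protocol article*

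**What the plan says.** The Protocol article describes the task under Outcome Measures, Behavioral Assessments. The experimenter "instructed the child to remain seated and not touch the bag until she returned". The wait is fixed: "After a 3-minute delay, the experimenter returned, placed the bow on the bag".

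Two things are scored. The first is a 1 to 5 score for resisting the bag. The second concerns the seat. It is introduced as time out of the seat, "categorized into 4 distinct levels", but the levels are defined by time in the seat: "1 for <30 seconds in the seat to 4 for >2 minutes in the seat". A higher level therefore means longer seated. The cut-offs around levels 2 and 3, beyond these two end points, are not given.

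The final seat score is then made by "assigning an additional half point for each minute a child spent out of the seat". Two conditions limit this credit: only time when the child could still reach the table counts, and only children scoring 1 or 2 receive it. The text gives no upper limit to this addition and does not say whether part-minutes count.

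**The concern.** The levels reward sitting, as the child was told to do. The addition rewards minutes not sitting, provided the child stays near the table. As partial credit for not wandering off, that is understandable. But the amount grows with time out of the seat, has no ceiling below the next level, and is withheld from level 3. Two children may both stay by the table throughout, and the one who sat for less time can then end with the same or a higher score.

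Self-regulatory capacity is part of the article's second aim, and this task is one of its measures. With 22 intervention and 10 control children, a few misplaced scores could matter to an analysis of this sub-score.

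**Working it through.** The article gives no figure to reproduce here, so the check applies the stated rule directly.

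**Inputs** (all from the gift delay description in Behavioral Assessments)
- Length of the wait: 3 minutes, or 180 s.
- Level 1: under 30 s seated. Level 4: over 120 s seated.
- Cut between levels 2 and 3: not stated. Values of 45, 60, 90 and 120 s were tried.
- Credit: 0.5 per minute out of the seat and within reach, for scores of 1 or 2, taken here as seat levels.
- Part-minutes: not stated. Both pro rata and whole-minute credit were tried.

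**Formula.** With *s* seconds seated and a share *r* of the remaining time within reach:
- levels 1 and 2: final = level + 0.5 × *r* × (180 − *s*)/60
- levels 3 and 4: final = level

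**All out-of-seat time within reach (*r* = 1)**

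| Seconds seated | Level | Pro rata credit | Whole-minute credit |
|---|---|---|---|
| 0 | 1 | 1 + 0.5 × 3.00 = 2.50 | 1 + 0.5 × 3 = 2.5 |
| 29 | 1 | 1 + 0.5 × 151/60 = 2.26 | 1 + 0.5 × 2 = 2.0 |
| 30 | 2 | 2 + 0.5 × 2.50 = 3.25 | 2 + 0.5 × 2 = 3.0 |
| 59 (cut at 60 s or later) | 2 | 2 + 0.5 × 121/60 = 3.01 | 2 + 0.5 × 2 = 3.0 |
| 119 (cut at 119 s or earlier) | 3 | 3.00 | 3.0 |

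**Between levels, pro rata.** Child A sits 30 s and spends 150 s within reach. Child B sits 119 s and spends 61 s within reach. Neither leaves the table area. A scores 3.25 and B scores 3.00. The 3.25 does not depend on the cut between levels 2 and 3, which must lie above 30 s.

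**How much time within reach this needs.** A level 2 child passes 3.00 when 0.5 × minutes within reach exceeds 1, that is, with more than 120 s within reach. For a child seated 30 s, that is more than 120/150 = 80% of the out-of-seat time. With half of it within reach, the score is 2 + 0.5 × 1.25 = 2.625 and level 3 is not passed.

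**Between levels, whole minutes.** A level 2 child seated 30 to 60 s has two full minutes out and reaches 3.0: a tie with level 3, not a pass.

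**How often, on a one-second grid.** Seated times from 0 to 180 s give 181 × 180/2 = 16,290 pairs. These are pairs of possible times, not children. With a cut at 60 s and everyone within reach, the shorter-seated child scores strictly higher in:
- pro rata: 435 pairs within level 1 + 435 within level 2 + 30 × 61 = 1,830 between levels 2 and 3, total 2,700
- whole minutes: 29 pairs, all of them 0 s against 1 to 29 s

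With whole minutes and a cut at 90 s there are 928 such pairs: the same 29, plus 31 × 29 = 899 within level 2, where 30 to 60 s gives 3.0 and 61 to 89 s gives 2.5.

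**If the condition refers to the bag-touch score.** Children who took the gift or put a hand in the bag would then get the credit at any seat level. If A and B both qualified, A would score 3.25 and B would score 3 + 0.5 × 61/60 = 3.51, so the comparison above does not carry over. Within any one seat level, the credit still rises with time out of the seat.

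**The case against.** The strongest defense is that the credit is conditional. A child who leaves the seat and walks away gains nothing, so the rule separates children who hover by the table from those who wander off. That stands, and it rules out one tempting inference: that leaving the seat earlier earns more in general. It does so only between children with the same behavior within reach. The defense does not explain why level 3 gets no credit for the same behavior, or why the credit may exceed the gap between levels.

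Second, passing level 3 requires pro rata credit. The wording fits whole minutes at least as well, and then the result is a tie. At a 60 s cut, the only strict whole-minute inversions involve a child seated 0 s, which is hardly attainable when the task begins with the child seated. This stands as a limit on size. The tie remains, and so do inversions within level 2 if the cut is later than 60 s.

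Third, a reader might say that the rule reverses an existing order within levels 1 and 2. It does not: before the credit, children in the same level are tied. What the rule does is break those ties against time seated when all stay within reach.

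Fourth, the article uses the word score for the bag scale and level for the seat categories, so the condition could refer to the bag score. The seat-level reading is the more natural one, but the text does not settle it.

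Finally, introducing the measure as time out of the seat and coding it as time in the seat is a slip of wording only, since the two are complements within a fixed 3 minutes.

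**Conclusion.** The concern holds for this sub-score. On the seat-level reading, the published rule can place a level 2 child who stayed within reach level with a level 3 child who sat longer and also stayed within reach (whole minutes, 3.0 each), or above that child (pro rata, up to 3.25 against 3.00). The pass needs more than two minutes within reach. On the bag-score reading, the direction of the credit is still awkward, but those figures do not apply.

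A reader might go further and infer that the trial's self-regulation contrast is compressed or inverted. The article does not support that. The bag-touch score is untouched, the seat score is one sub-score of one of four behavioral tasks, and nothing shows how many children fall in levels 1 or 2 or how long they stayed within reach. The rule may also be a reporting slip for a different formula. Even so, anyone scoring from the text would get the misordering, so the text should be corrected.

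**What to change.** - Rescore from the existing timings and recordings. Use seconds in the seat as the score for every child, with seconds in the seat or within arm's reach as a second variable, so that the information on proximity is kept.
- If the 1 to 4 levels are kept, give the credit at every level as the share of out-of-seat time spent within reach, capped below one level so that it cannot lift a child to or past the next. For example, with a maximum of half a point, child A would score 2.5 and child B 3.5. A child who never leaves the seat has no out-of-seat time to divide by, so that case needs a stated value, such as the full credit.
- State which score the condition refers to, the cut between levels 2 and 3 and, if the present formula is retained anywhere, how part-minutes count. Correct the lead sentence to time in the seat.

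The cost is a little rescoring and a departure from the published composite. No new data are needed. Time within reach may have been noted only for children who qualified for the credit, so the others may need a look at the video. The article says that data are still being processed (Results) and that video files will be destroyed at the end of the study (Ethical Considerations), so this should be done before then.

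### Go/no-go scoring: the nonresponsiveness rule joins its two conditions with 'or', so blocks with perfect withholding are deleted and the impulse control score is capped at 0.80

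*Protocol article*

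**What the plan says.** The protocol article (Outcome Measures, Behavioral Assessments) gives the full scoring sequence for the go/no-go task.

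- Purpose: "The go/no-go task assessed inhibitory control in young children". High accuracy on no-go trials is therefore the good result.
- Trials: "80% (n=60) of the trials were “go” trials and 20% (n=15) were “no-go” trials", and "The main task consisted of 75 test stimuli evenly distributed across 3 blocks".
- Step 1, trial exclusion: "Scores were calculated by first excluding trials with response times <300 millisecond".
- Step 2, block exclusion for nonresponsiveness: "blocks were removed if the child demonstrated nonresponsiveness (ie, go trials with <20% accuracy or no-go trials with >80% accuracy"). The two conditions are alternatives.
- Step 2, block exclusion for indiscriminate responding: "indiscriminate responding (ie, go trials with >20% accuracy and no-go trials with <20" per cent. Here both conditions must be met.
- Step 3, the impulse control score is "calculated by multiplying the percentage of correct “go” responses by the percentage of correct “no-go” responses".

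Nothing elsewhere in the article restricts the no-go condition to blocks with low go accuracy.

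**The concern.** A child who has stopped responding leaves a recognisable pattern: few correct go trials and, because nothing is tapped, nearly all no-go trials correct. The pattern is the conjunction. Either half alone means something else, and high no-go accuracy with high go accuracy is the best performance the task allows. The written rule classes that performance as invalid.

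Two things follow. The outcome has a ceiling that its formula does not imply. And whether a block is missing depends on the quantity being measured, with the risk rising as inhibitory control improves. Self-regulatory capacity is a target of the second aim (Effects on Mechanisms and Outcomes), to be tested by t tests and regression (Data Analysis) on 22 intervention and 10 control children. If the program improves inhibition, the intervention arm loses more blocks and more children, and its remaining scores are pulled down. The comparison is biased toward no effect, and missingness differs by arm.

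**Working it through.** **Inputs from the article.** 60 go and 15 no-go trials, 75 stimuli, 3 blocks. Check: 60/75 = 80%, 15/75 = 20%, 75/3 = 25 per block. These agree with the stated mix.

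**Assumptions.** 20 go and 5 no-go trials per block (the article gives only the even split of the 75 stimuli), independent trials, and no trials lost to the 300 ms rule. The article reports no observed accuracies, so the true no-go accuracy *p* is varied.

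**1. What the rule keeps.** With 5 no-go trials, accuracy can be 0, 20, 40, 60, 80 or 100%, so above 80% means 5 of 5. There are 21 × 6 = 126 possible block results (0–20 go correct, 0–5 no-go correct).

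- As written ('or'): 17 go counts (4 to 20) × 4 no-go counts (1 to 4) = 68, plus the single result of 4/20 go with 0/5 no-go, which neither rule catches. Total kept: 69. The maximum score is 1.00 × 0.80 = 0.80. A block with 20/20 go and 5/5 no-go is removed.
- With 'and': removed are 4 × 1 (go 0–3, no-go 5/5) and 16 × 1 (go 5–20, no-go 0/5), so 126 − 20 = 106 are kept. The maximum score is 1.00, and the perfect block is kept.

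**2. Dependence on 5 per block.** The cap needs no such assumption: any retained block has no-go accuracy of at most 80%. Checking 1 to 9 no-go trials per block, a fully correct block is always removed; with 6 to 9, a block with one error is removed too.

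**3. How often blocks are lost.** P(5 of 5) = p^5, and P(all three blocks removed) is approximately (p^5)^3 = p^15. With go accuracy set at 90% and both exclusion rules applied:

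| True no-go accuracy | P(block removed) | P(all 3 removed) | Expected score, kept block | True score |
|---|---|---|---|---|
| 0.60 | 0.09 | 0.001 | 0.515 | 0.54 |
| 0.70 | 0.17 | 0.005 | 0.577 | 0.63 |
| 0.80 | 0.33 | 0.035 | 0.633 | 0.72 |
| 0.90 | 0.59 | 0.21 | 0.680 | 0.81 |
| 0.95 | 0.77 | 0.46 | 0.701 | 0.855 |
| 1.00 | 1.00 | 1.00 | none | 0.90 |

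With 'and', at most 1% of blocks are removed over this range, and from 0.80 upward the expected score equals the true score.

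**4. Effect on a group difference.** Mean no-go accuracy in retained blocks is (p − p^5)/(1 − p^5).

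- p = 0.75: (0.75 − 0.2373)/(1 − 0.2373) = 0.672.
- p = 0.90: (0.90 − 0.5905)/(1 − 0.5905) = 0.756.
- Apparent gain 0.084 against a true 0.15, so attenuation is 1 − 0.084/0.15 = 44%.

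The same 15-point gain from 0.60 to 0.75 is attenuated by 29%, and from 0.50 to 0.65 by 20%. Including the removal of 0/5 blocks, these two become about 33% and 28%.

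**5. Loss of children.** If all children did the task, at p = 0.90 about 22 × 0.206 = 4.5 intervention children would have no score. At p = 0.75 about 10 × 0.75^15 = 10 × 0.013 = 0.13 control children would have none.

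**The case against.** The strongest reply is that this is probably a slip of wording. The label 'nonresponsiveness', the 'and' in the parallel rule and the purpose of the score all suggest that the authors meant 'and', and the article shows neither the scoring code nor a count of removed blocks. That is fair: the document cannot establish that data were in fact lost. But it reports the rule, in the past tense, as the one applied, and action is needed either way. If the code used 'or', the scores are distorted. If it used 'and', the published rule is wrong and could be carried into the planned full-scale trial.

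The size is also open to challenge. The 44% comes from one scenario near the upper end of the scale; the 80/20 mix was chosen to make inhibition harder and the children are 3 to 5 years old, so lower accuracies and attenuation of 20% to 33% are plausible. This stands, and the figures should be read as a range. Five no-go trials per block is likewise an assumption, but only the percentages depend on it, not the deletion of perfect blocks or the cap.

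Finally, this is one of four behavioral tasks in a feasibility pilot, it is not named as primary, and the other three tasks are untouched. That limits the reach of the error but does not make the rule right.

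**Conclusion.** The concern holds for the rule as written. It deletes every block with perfect withholding, caps the impulse control score at 0.80 whatever the number of no-go trials per block, and leaves a child who is perfect on all no-go trials without a score. Assuming 5 independent no-go trials per block, a block is lost with probability 0.33 at a true no-go accuracy of 0.80 and 0.59 at 0.90. A true 15-point difference shrinks by roughly 20% to 44%, depending on where on the scale it lies. These percentages are illustrative because no observed accuracies are reported, and the bias is real only if the code followed the text. The reach is one of four behavioral tasks in a pilot, but for that task the error affects validity and should be settled before the arms are compared.

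**What to change.** 1. Check the scoring code for the operator actually used.
2. Restate the nonresponsiveness rule so that a block is removed only when go accuracy is below 20% **and** no-go accuracy is above 80%.
3. If the code used 'or', rescore all time points from the trial-level data before any arm comparison. If it already used 'and', only the text changes.
4. Report the number of blocks removed under each rule, and the number of children left without a score, by arm and time point.
5. While editing, assign the boundary case of exactly 20% go accuracy with low no-go accuracy, which currently falls under neither rule.

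The cost is a one-word change and a re-run of the scoring. No new data are needed, and the Results section says the data are still being processed for analysis.
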